## Abstract

**Background:**

Rural residents generally lack adequate physical activity to benefit health and reduce disparities in chronic diseases, such as cardiovascular disease and certain cancers. The Socioecological Model describes physical activity as involving a dynamic and reciprocal interaction between individual, social, and community factors. Community group-based walking programs and civic engagement interventions aimed at enhancing physical activity have been successful in rural communities but have not targeted all three socioecological levels. Public libraries can act as innovative public health partners in rural communities. However, challenges remain because rural libraries often lack the capacity to implement evidence-based health promotion programming. The goals of this study are (1) build the capacity for rural libraries to implement evidence-based health promotion programs, (2) compare changes in physical activity between a group-based walking program and a combined group-based walking and civic engagement program with rural residents, and (3) conduct an implementation evaluation.

**Methods:**

We will conduct a comparative effectiveness study of a group-based walking (standard approach) versus a group-based walking plus civic engagement program (combined approach) aimed at enhancing walkability to increase physical activity among rural adults. Key mediators between the program effects and change in outcomes will also be identified. Finally, we will evaluate program implementation, conduct a cost effectiveness evaluation, and use a positive deviance analysis to understand experiences of high and low changers on key outcomes. Twenty towns will be matched and randomized to one of the two conditions and our aim is to enroll a total of 350–400 rural residents (15–20 per town). Study outcomes will be assessed at baseline, and 6, 12, and 24 months.

**Discussion:**

This study will build the capacity of rural libraries to implement evidence-based walking programs as well as other health promotion programs in their communities. The study results will answer questions regarding the relative effectiveness and cost effectiveness of two multilevel physical activity interventions targeting rural communities. We will learn what works and how these multilevel interventions can be implemented in rural populations.

**Trial Registration:**

ClinicalTrials.gov Identifier: NCT05677906.

**Supplementary Information:**

The online version contains supplementary material available at 10.1186/s12889-023-16788-0.

## Background

Engaging in the recommended amount of physical activity (150 min per week of moderate level activity) has numerous health benefits, including lower risk of chronic diseases, such as heart disease and diabetes and some types of cancer [1]. Worldwide, achieving enough physical activity could prevent upwards of 5.3 million deaths per year [2]. Despite this evidence, nearly 75% of US adults fail to achieve adequate levels of physical activity [3]. Rural residents are less likely to meet recommended levels of physical activity compared with their urban counterparts [4] and tend to have higher rates of obesity, cancer and heart disease compared with their urban counterparts [5–7]. Walking is the most common form of physical activity [8–10], and people who walk are more likely to meet recommended levels of physical activity compared to non-walkers [8]. However, rural residents compared with urban residents report walking less [11]. The persistence of this rural-urban disparity in physical activity suggests a need for effective interventions for rural communities.

The Socioecological Model (SEM) is a framework for understanding determinants of health behaviors including physical activity. The model emphasizes the reciprocal interplay among multiple levels of influence: individual, social, and community [12]. The SEM is consistent with social cognitive theory (SCT), which posits that health behavior is based on the dynamic and reciprocal interaction between individual (e.g., self-efficacy, self-monitoring), social (e.g., modeling, support, cohesion), and environmental (e.g., built environment) factors. Interventions designed to promote physical activity are likely to be most effective if they target individual, social, and community factors [12]. In 2015, the US Surgeon General issued a *Call to Action* to promote walking and walkable communities highlighting the importance of walking and having safe places to walk [13]. Recognizing the impact of the environment on health, the Centers for Disease Control and Prevention recommend changing the social and built environments to make the healthy choice easier [14].

Community group-based walking programs have been shown to increase walking, physical activity, and fitness and improve health outcomes, including with rural communities [15–18]. Walking groups that last longer than six months have been found to have larger effect sizes, suggesting that benefits appear to be durable over time [19, 20]. Group-based walking programs address social influences of physical activity by building group cohesion, social support, and social capital to promote adoption and maintenance of walking for health [18, 21, 22]. In rural communities, social support (or lack of social support) can be an important facilitator (or barrier) for walking [23–25], and group-based walking programs can strengthen social networks and improve social support [26, 27]. The built environment (e.g., sidewalks, traffic) is also associated with walking [28, 29]. Walking groups can impact perceptions of the built environment [30] and aspects of the built environment can influence adherence to walking program [31, 32].

Civic engagement is one approach to built environment change, such as enhancing walkability. Civic engagement refers to individuals participating in the community in order to improve the conditions of the community [33]. Civic engagement for built environment change focuses on the social and community factors and can improve local built environment and policies related to community physical activity [34–36]. At the interpersonal level, civic engagement builds social support and collective efficacy to accomplish community change [37].

Relative to urban communities, rural communities generally lack the necessary resources to implement public health programming. An innovative public health partner in rural communities is public libraries, which are increasingly offering a multitude of programs [38–43]. A 2017 survey found that 42% of libraries surveyed offered general walking, hiking, bicycling, or running programs [40]. Libraries are also implementing initiatives to engage community members in civic engagement [44]. Although libraries may be ideal institutes to lead civic engagement efforts, no published studies of civic engagement for walkability have been based in libraries since libraries often lack the capacity to implement evidence-based programming. Capacity building is one strategy that can address this gap and provide support to libraries for implementation and evaluation so that programs reach the intended population and achieve the desired results [45].

Although rural residents face greater health disparities compared to urban residents in terms of chronic disease, there is a major gap in achieving reach and sustainable impact in behavior changes to reduce the risk of these diseases. Multilevel physical activity interventions are likely to be more effective, but there is limited evidence on how they work with rural communities, which often lack the capacity to conduct and sustain these interventions. Thus, disparities in rural physical activity persist. This study addresses this gap by comparing the effectiveness of multilevel physical activity programs that promote walking in rural communities and identifying key mediators of the program. The aims of this study are (1) increase the capacity of rural libraires to deliver evidence-based health promotion programs, (2) compare the effects of a group-based walking program with a combined group-based plus civic engagement program on physical activity, cardiovascular fitness and collective efficacy among rural residents, 2a) identify key mediators between the intervention program effects and change in physical activity, fitness, and collective efficacy, and (3) evaluate program implementation and cost effectiveness.

## Methods

### Design and setting

This study is a comparative effectiveness experiment of a group-based walking program, Step It Up!, versus a combined program of both Step It Up! (SIU) and a civic engagement program aimed at walkability, the Change Club. We also will conduct a mixed-method implementation evaluation. At the organizational level (library), a prospective convergent parallel mixed methods design [46] will be used, in which quantitative and qualitative data will be collected in parallel, analyzed separately, and merged in order to gain a full understanding of factors that influence implementation and sustainability of the program in the libraries. At the participant level, a positive deviance approach will be used to understand experiences of high and low changers on outcomes. A sequential mixed methods design [46] will be used, with quantitative participant outcomes informing selection of participants for qualitative work.

This study will take place in 20 rural communities in Oregon. The US Institute of Museum & Library Services (IMLS) classifies libraries as serving urban, suburban, town, or rural areas using the National Center for Education Statistics (NCES) definitions for each classification [47]. The library’s classification is based on the geocoded latitude and longitude of the library’s address. For this study, libraries serving towns and rural areas are eligible. The NCES, drawing upon the U.S. Census, defines towns as areas outside of urbanized areas, but inside towns with populations between 2,500 and 50,000. This grouping of rural and town libraries follows the standard practices of libraries, as seen in organizations like the Association for Rural & Small Libraries.

The rural communities in which the libraries are located will be matched on population, median household income, percent of residents who identify as white, walk score, rate of violent crime, percent of population 65 years or older, employment rate, percent residents without health insurance, and area deprivation index. Matched pairs will then be randomized to either a group-based walking program, Step It Up! (SIU) or the combined program (Combined) that includes both SIU and a civic engagement program, Change Club. Cluster (pairs) randomization will be implemented using the Goldilocks approach [48]. This approach involves iteratively choosing pairs that minimize distance with respect to potential confounding variables, visually assessing differences across possible randomizations, and reweighting variables by selecting confounder weights. The best pair matching was achieved by unit weighting (given weight = 1) all confounders except for population (weight = 3), walk score (weight = 3), area deprivation index (weight = 3), and percent white only (weight = 2). Libraries will be randomized prior to the start of the capacity building and training so that librarians in the SIU group are not exposed to the Change Club curriculum.

We will disseminate results to the scientific community through peer reviewed publications and presentations and to the communities through presentations and written materials, such as an infographic.

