### Study aims and approaches

#### Aim 1

Increase the capacity of rural libraries to deliver evidence-based health promotion programs

Capacity building will start pre-program implementation to get the libraries ready for implementation and will continue throughout implementation. We will provide the 20 librarians with technical assistance on program implementation and $5,000 stipends to support program implementation. Librarians will be divided in two groups based on the randomization, a SIU group and a Combined group and will attend trainings and webinars with their group. We will hold two 60-minute trainings for the SIU program and an additional 60-minute training for the Combined program prior to program implementation. All librarians will receive a SIU Toolkit that provides information on how to set up and deliver a group-based walking program as well as handouts for participants. Librarians in the Combined Program will be given a facilitator guide and curriculum for the Change Club and handouts for participants. Additionally, the Change Club groups will be awarded $5,000 after submitting a budget for use of the funds. We will hold monthly webinars to provide an opportunity for the librarians to learn from and support each other as they plan for and implement the programs. The research team will be available via phone calls or email to librarians throughout the study for questions or individualized support as needed. Each librarian will complete the Public Health Professional Competency Assessment [49] prior to the trainings and at the end of the two-year study.

#### Aim 2

Compare the effects of a group-based walking program with a combined group-based plus civic engagement program on physical activity, cardiovascular fitness, and collective efficacy among rural residents.

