The implementation evaluation is based upon the Consolidated Framework for Implementation Research (CFIR) and the Socioecological Model (SEM). The CFIR, derived through a comprehensive synthesis of the implementation literature [83], has five domains: inner setting, outer setting, characteristics of individuals involved, implementation processes, and intervention characteristics. Together, CFIR and the SEM will guide the assessment and help identify factors influencing implementation and intervention effectiveness. Table 4 outlines the CFIR domains and data sources. We expect a complex set of factors will distinguish high-versus-low change in study process and outcome measures. We will identify what influences the extent to which a library is able to implement SIU or Combined program and participants are able to make and maintain behavior changes. We will identify setting/organization (e.g., organizational culture, leadership) and participant (e.g., resources, priorities) factors that distinguish high/low-change among participants and why. We will identify key organizational and local factors that contribute to sustainability and scale-up [84].

**Table 4 Tab4:** Implementation evaluation

CFIR Domains & Constructs	Measures/Data Sources (Timing)
***Program Characteristics*** Complexity; design; adaptability; sustainability; cost; relative advantage	• Cost analysis • Surveys: librarians (3, 6, 12 months) • Interviews: librarians (6 months) • Observations: walks/sessions, webinars
***Inner Setting*** Climate, relative priority, compatibility, leadership	• Surveys: librarians (3, 6, 12 months) • Interviews: librarians (6 months) • Observations: walks/sessions, webinars
***Outer Setting*** Participant resources, needs, facilitators & barriers; cosmopolitanism; built environment/policy	• Surveys: librarians (3, 6, 12 months), participants (baseline, 6, 12, 24 months) • Interviews: librarians (6 months), participants (high & low changers, 6, 12, 24 months) • Attendance records • Observations: walks/sessions, webinars
***Individual Characteristics*** Knowledge; attitudes & beliefs; personal attributes	• Surveys: librarians (3, 6, 12 months) • Interviews: librarians (6 months) • Observations: walks/sessions, webinars
***Process*** Planning; engaging; executing; reflecting; evaluating	• Surveys: librarians (3, 6, 12 months) • Interviews: librarians (6 months) • Observations: walks/sessions, webinars • Recruitment & retention tracking

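### Table 4 dates no pre-program survey or interview for library climate, priority, leadership or librarian attitudes, so ratings offered as influences on early implementation may partly reflect it (Aim 3 only, optional)

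*Protocol article*

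**What the plan says.** Under Design and setting, the protocol article describes a prospective mixed-methods evaluation at library level, intended "in order to gain a full understanding of factors that influence implementation and sustainability of the program in the libraries". The Aim 3 text goes further. It undertakes to identify what influences how far a library can implement its program, which setting and participant factors separate high from low change, and which organizational factors contribute to sustainability and scale-up. Organizational culture and leadership are given as examples.

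Table 4 sets the data sources. The inner-setting constructs are "Climate, relative priority, compatibility, leadership" and the individual-characteristics constructs are "Knowledge; attitudes & beliefs; personal attributes". For both, as for the other three domains, the dated librarian sources are "Surveys: librarians (3, 6, 12 months") and "Interviews: librarians (6 months"). Observations of walks, sessions and webinars are listed without dates. In the outer-setting row, participants are surveyed at "participants (baseline, 6, 12, 24 months").

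Under Aim 1 there is one earlier librarian measure: "Each librarian will complete the Public Health Professional Competency Assessment [49] prior to the trainings and at the end of the two-year study".

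**The concern.** To say that an organizational factor influenced implementation, one needs its value before implementation could have acted on it. By the first dated survey librarians have been trained, presumably have received the $5,000 stipend, and on the natural reading have led weekly walks for three months. A librarian whose group is thriving may then rate the library's climate, its priority for the program, or their own beliefs about it more favourably. A librarian whose group is struggling may do the opposite. A difference between well and poorly implementing libraries could then be read as climate producing success when it partly runs the other way.

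Capacity building is itself an intervention under Aim 1. It could shift these constructs before anyone records them, and no change from a pre-program value could be computed. What is at stake is the list of factors put forward for scale-up: some could be consequences of good delivery rather than conditions for it.

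**Working it through.** No arithmetic applies and the plan gives no figure to reproduce. The check sets the stated schedule beside the stated purpose.

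| Source | Dated timing | Before training? | Covers climate, priority, leadership, attitudes? |
|---|---|---|---|
| Librarian survey (Table 4, all five domains) | 3, 6, 12 months | No | Yes |
| Librarian interview (Table 4, all five domains) | 6 months | No | Yes |
| Observations of walks, sessions, webinars (Table 4) | None given | Unclear for webinars | Listed as a source, content not stated |
| Competency assessment (Aim 1) | Before the trainings; end of the two years | Yes | Not stated; not in Table 4 |
| Participant survey (Table 4, outer setting) | Baseline, 6, 12, 24 months | Baseline wave | Not a librarian source |

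1. *Count of pre-program waves.* Of the four dated librarian waves in Table 4 (three survey times and one interview time), none precedes the program on the natural reading of the months.

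2. *Is this only condensation?* Table 4 does print a baseline where one is planned, for participants. The librarian entry is a stated schedule that starts at month 3.

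3. *What does month 3 count from?* Table 4 does not say, and the schedule figure is not available here. Program start is the natural reading, because 6 and 12 months coincide with the participant timepoints. If the months ran from the start of capacity building instead, the first survey would still fall after that support began.

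4. *Which conclusions are exposed?* High and low changers are first identified after six months, and sustained change is judged at 12 and 24 months. The month-3 rating therefore precedes these points by 6 − 3 = 3, 12 − 3 = 9 and 24 − 3 = 21 months. Delivery in the first three months can feed into that rating; later events cannot. Exposure is greatest for early implementation and weaker for sustainability. It does not vanish there, because early success may persist and so be linked to both the rating and the later result.

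5. *What will be done with the ratings?* The Aim 3 quantitative analysis is confined to descriptive statistics. The qualitative analysis then compares cases, looks for factors that discriminate between them, and builds a matrix of factors present or absent. No test of a library factor against implementation is planned, so there is no formal estimate whose bias could be computed. The time-order problem enters when the comparisons are put into words.

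**The case against.** Four points on the other side carry weight.

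- **Some pre-program information exists.** A reader might infer from Table 4 that nothing is measured on librarians beforehand. The documents do not support that: every librarian completes the competency assessment "prior to the trainings and at the end of the two-year study". Webinars are meant to help librarians plan as well as implement, so some webinar observations may precede delivery. Neither fills the gap. The assessment is not said to cover climate, leadership or attitudes, and the webinars are undated sessions held by arm, not a library-by-library record.
- **The month-3 rating is prospective for later results.** A reader might infer that every association between library factors and outcome is open to reverse causation to the same degree. It is not: the ratings precede the 6-, 12- and 24-month results, and groups become peer-led only after six months. This stands, and it confines the concern mainly to early implementation.
- **The analysis is descriptive and triangulated.** A reader might picture inflated false-positive rates. No such test is planned, the strength of any feedback from success to rating is unknown, and findings are to be checked against other sources and with participants. This also stands, so no error rate should be attached to the point.
- **Some items cannot be asked early.** Compatibility concerns the fit of a program that the librarian has not yet been taught. This stands and limits the remedy.

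The full protocol may also hold readiness or site-selection data that the article omits. That is possible, but the article's own table states when the librarian surveys occur.

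**Conclusion.** The point holds in a limited form. For climate, relative priority, leadership, and librarian attitudes and beliefs, the first dated measure is the 3-month survey, while the text promises to identify what influences implementation. For early implementation the order of cause and effect cannot be established from these ratings. For sustainability the order is better supported, though not secured.

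The size is qualitative: a risk of over-reading in one descriptive aim covering 20 libraries. The randomized comparison, the primary outcomes and the cost-effectiveness analysis do not depend on it. The conclusion assumes that the months count from program start and that the competency assessment does not measure organizational climate or leadership. Both are natural readings, but the article confirms neither. Severity is optional.

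**What to change.** - Give the general inner-setting and individual-characteristics items of the librarian survey once before training, at the contact where the competency assessment is already completed. For those two rows Table 4 would then list librarian surveys at baseline, 3, 6 and 12 months.
- Keep program-specific items, such as compatibility, from 3 months onward.
- State in the Aim 3 text that baseline ratings are the candidate determinants of implementation and that the 3- to 12-month ratings are process measures.

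The cost is one short extra survey for 20 librarians at an existing contact, with no change to arms, outcomes or participant burden.

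If training has already begun, the baseline cannot be recovered. In that case, report associations between the 3- to 12-month ratings and implementation as non-directional, and do not use the competency score as a substitute for climate or leadership. That costs only wording.
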